#### Experimental condition: MAT + A-CHESS

Patients in the experimental condition will receive a smartphone with A-CHESS for 16 months along with MAT as described above. A-CHESS is designed to improve recovery from addiction. A-CHESS is based on self-determination theory (SDT), which holds that meeting three needs—for autonomy, competence, and relatedness—improves a person’s adaptive functioning [35, 37]. Figure 2 shows how A-CHESS services relate to the constructs of SDT and to the determinants and antecedents of relapse identified by Marlatt [16, 38, 39]. A-CHESS services provide antecedent-appropriate intervention(s) that boost autonomy (intrinsic motivation) by selecting from multiple services those most likely to be most personally meaningful to the patient; offer information, monitoring, and tools to increase competence; and/or increase relatedness. For example, the lower part of Fig. 2 shows antecedents of relapse, one of which is lifestyle imbalance (lower left of figure) and Marlatt’s suggestion that developing substitute indulgences helps (second level-left). The left upper section shows how A-CHESS helps. Another example: A-CHESS monitoring tools include a weekly check-in and GPS-based tracking to identify when lifestyle imbalance may place a patient at risk of using drugs or engaging in unsafe sex. As one healthy alternative, the A-CHESS healthy events calendar may suggest one of the patient’s healthy pleasures, such as going for a walk, and offer a map. We anticipate that this just-in-time approach may be important to help maintain abstinence. Figure 3 shows the A-CHESS user interface. Key A-CHESS services are described below.

**Fig. 2 Fig2:**
[figure not shown]
Overview of patient-facing A-CHESS services

**Fig. 3 Fig3:**
[figure not shown]
A-CHESS user interface

Help. When a patient presses *Help*, the system shows a list of the patient’s preapproved supporters and their phone numbers so the patient can easily call for help. The patient can also be linked to positive and potentially distracting activities such as selected games [40] and audio/video-based relaxation recordings [41].

Cognitive behavioral therapy (CBT) boosters offer brief, easy-to-remember reviews of CBT skills that patients learned during treatment to prepare them for future challenges—e.g., how to handle urges and anticipating, avoiding, and mitigating the effects of high-risk people, places, and things related to past drug use.

Monitoring functionality includes the location tracker (described below), self-assessment tools, and a record of A-CHESS use. One self-assessment tool is the Brief Addiction Monitor (BAM) [42], which we implement as a weekly survey. After completing the BAM, participants receive tailored feedback that acknowledges their use of protective behaviors over the past week and provides recommendations for addressing risky behaviors, including links to appropriate A-CHESS content. Participants reporting opioid or other drug use will be encouraged to seek appropriate help.

The location tracker uses GPS to monitor patient movement. If a patient approaches a location that they previously defined as high risk, A-CHESS will initiate a patient-defined recovery process. This might start with a beep, then a vibration, and then a list of preapproved contacts and options for distraction or mindfulness. The GPS service is also often used to find a 12-step meeting. Patients may turn off the location tracker if they perceive certain services to be too burdensome or invasive.

Triage and feedback functionality is designed to derail the relapse process, giving the patient just-in-time, tailored coping support. A-CHESS will be customized at the start by each patient to set options that will be triggered in a moment of need. For example, if a patient reports a craving triggered by environmental cues, such as seeing someone else use, A-CHESS might remind the patient of relaxation exercises, connect them to online peer support and the healthy events calendar, and/or notify a counselor, who may initiate contact via text or private message. Participants whose patterns of using A-CHESS demonstrate they are likely to stop using the system will receive automated messages and tailored messages from coaches to encourage them to reengage.

The counselor dashboard [43], developed by addiction physicians and psychologists, harvests clinically relevant data from A-CHESS and presents it to counselors to help them quickly: (1) identify patients who may be at high risk for relapse and/or benefit from clinical intervention, (2) see a detailed analysis of a patient’s recent history, e.g., trends in individual BAM items, A-CHESS use, and relapse data, and (3) intervene with patients (e.g., through texting in A-CHESS). When a counselor logs into the counselor dashboard, he sees ‘red pins’ generated when A-CHESS (using counselor-determined priorities) detects that a patient may be at high risk. The counselor can adjust the cutoffs for red pins so the ones he sees are most useful.

HIV/HCV services. A-CHESS will integrate components of our team’s existing computerized risk reduction systems that collect data on patients’ HIV/HCV risk behaviors and deliver behavior change interventions tailored to the patient’s self-reported readiness for change. At enrollment, participants in both study conditions will be asked if they have been screened for HIV and HCV. Patients who test negative or decline testing at baseline will be sent reminders from A-CHESS about future testing at a frequency based on reported risk behaviors. Patients found to be HIV or HCV-positive will be provided with targeted multimedia health education content, access to online resources, and location-specific links to clinical care and case management.

Coach-monitored discussion groups [44] foster the exchange of emotional, informational, and instrumental support among patients. Discussions are monitored daily by an A-CHESS coach to encourage appropriate use. Coaches are not counselors, but are members of the research team trained on A-CHESS, risk identification, referral, and technology-based patient engagement. They are skilled in constructive interaction and persistence and are willing to work unusual hours. The coaches encourage individuals to follow up with their health care providers/prescribers regarding medication-assisted treatment questions. We found that a coach increases and sustains use of A-CHESS [45]. Every week, a coach reviews use data. Based on what the coach sees, they write messages to the participants. For example, (1) to a patient active on A-CHESS, “Hi [name], Just wanted to say hello and see how things are going. Looks like you are doing a great job of recovery and tracking, which is wonderful. Let me know if there is anything I can help with. Take care and keep it up! [name].” and (2) to a patient who is not logging in: “Hi [name], Just checking in to see how you are coming with your recovery goals. You have not logged in for a while so I figured I would say hi. Take care and let me know what I can do to help! [name].”

Possible counselor alerts. A-CHESS sends an email notification to an A-CHESS coach if a patient reports substance use or is over a preset risk threshold on self-monitoring items. The coach may alert a counselor or encourage the patient to seek further support within A-CHESS (e.g., by using discussion groups, games, and relaxation exercises; revisiting their personal recovery motivation; or listening to personal stories from others in recovery) or recommend that the patient seek other professional help.

### Ethics

The study received approval from the Health Sciences Institutional Review Board at the University of Wisconsin-Madison (#2015-1418) and the Western Institutional Review Board (#1163410) in Puyallup, Washington and is registered at ClinicalTrials.gov (NCT02712034). The study complies with the relevant Standard Protocol Items: Recommendations for Interventional Trials (SPIRIT) Statement and World Health Organization Checklist (see the SPIRIT Checklist and figures in Additional files 1 and 2). The study is funded by the United States Department of Health and Human Services National Institute on Drug Abuse.

### Patient eligibility

Patients will be recruited from outpatient detoxification and treatment programs at three sites, two in Massachusetts and one in Wisconsin. Patients are eligible for the study if they (1) are currently on MAT (methadone, injectable naltrexone, or buprenorphine) for their substance use disorder (SUD), (2) are aged 18 years or older, (3) meet criteria for having an OUD of at least moderate severity (4 or 5 *Diagnostic and Statistical Manual of Mental Disorders, fifth edition* (DSM-V) criteria), (4) have no acute medical problem requiring immediate inpatient treatment, (5) have no history of psychotic disorders, though patients with other comorbid psychopathology (mood disorders, anxiety, other substance use disorders) will be eligible, (6) are willing to participate in a randomized clinical trial, (7) provide the name, verified phone number, and address of at least two contacts willing to help locate the patient, if necessary, during follow-up, (8) are able to read and write in English, (9) are not pregnant, (10) are willing to share health-related data with primary care clinicians, and (11) are, at study intake, abstinent from opioids for at least 1 week and no longer than 2 months, except for medications used to treat the disorder.

### Recruitment

Potential subjects will be identified by a staff person at each of the three sites and asked if they are interested in learning about a study for which they may be eligible. If they answer yes, the University of Wisconsin (UW) or site coordinator will provide a detailed overview of the study, including patient responsibilities and how patient confidentiality will be protected. Interested patients will then provide informed consent, complete a baseline survey, be randomized to receive MAT + A-CHESS or MAT, and, if applicable, be trained on A-CHESS. Figure 4 shows the flow of participants through the trial.

**Fig. 4 Fig4:**
[figure not shown]
Participant flow

### Randomization

The project director will use a computer-generated allocation sequence to randomize participants in a 1:1 ratio to MAT + A-CHESS or MAT alone, stratifying on gender and site and balancing on age, level of care (intensive outpatient treatment, day treatment, or weekly or monthly counseling), and whether patients had prior SUD treatment. The project director will inform the site coordinator of the group assignment by email; in the email, the participant will be identified only by study ID (the code used to make the identity of participants unknown). The site coordinator will initiate patients into the study condition and, if the patient is assigned to MAT + A-CHESS, provide training.

### Smartphone distribution

Patients randomized to MAT + A-CHESS who do not already have an Android smartphone will be given one loaded with A-CHESS, along with a data plan that includes unlimited data, text, and voice for 16 months. Patients who already have an Android smartphone will have A-CHESS installed on their phone. We will provide up to one replacement phone to patients who report their phone lost, stolen, or broken. If patients lose the second phone, we will offer to load A-CHESS onto an appropriate replacement smartphone (e.g., Samsung S5) that they obtain. We have included in the budget a 20% allowance for replacement phones, which has proven sufficient in prior CHESS research, including trials with populations of addicted patients [33, 46].

### Training to use A-CHESS

The UW or site coordinator will train patients to use the A-CHESS app and customize it − e.g., by sources of support (such as family), contacts who detract from recovery (such as friends who use illegal drugs) and support recovery, and so on. A-CHESS will be updated monthly with activities for the healthy event calendar; changes, if any, to therapeutic goals and the recovery plan (e.g., self-help groups, medication) and in home, work, or educational responsibilities; and high-risk locations to avoid. Patients must demonstrate that they can use A-CHESS (e.g., make one post to the discussion group) before they leave the training session with the phone.

### Quantitative data collection

All subjects will complete follow-up surveys over the phone with the UW study coordinator at months 4, 8, 12, 16, 20, and 24. Data collected will relate to the variables shown in Fig. 1. Each phone survey is expected to take 20 to 30 min. Surveys will be identified by study ID, not participant name. The form linking study IDs and names will be kept in REDCap [47]. In addition, urine screens, which are done routinely as part of MAT, will be conducted at each study site and recorded for all subjects at baseline and up to twice a month thereafter. Results will be used to validate self-reported information. Inconsistent results between urine drug tests and self-report results will not affect patients’ ability to continue in the study.

### Qualitative data collection

We will administer in-depth interviews with patients to shed light on their perspectives as well as on what promotes and hinders implementing and sustaining MAT + A-CHESS. We will explore patient perceptions of the effects of integrating MAT + A-CHESS, the most and least useful services in A-CHESS, gender-specific effects, and how patients feel about various A-CHESS services over time. A second set of interviews will examine provider perceptions of benefits of and barriers to integrating and sustaining MAT + A-CHESS over time. A third set of interviews will examine fine-tuning MAT + A-CHESS; communication between the research team, patients, and providers; and concerns from providers and patients. These data will help to refine methods for developing mHealth systems generally.

UW research staff will also conduct a longitudinal case study of five female and five male patients to explicate MAT + A-CHESS effects, considering patients’ medical and addiction treatment history, family history, personal and gender-specific preferences, and environmental factors. Case studies, though underused in health care [48], are a good way to understand how innovations work in real life [49]. They provide insight into patterns that might be overlooked in RCTs because they reveal the complexities of systems in which innovations are introduced. By following these ten individuals over time, we will explore how women and men integrate new technologies into their lives, circumstances that favor or complicate the process, and barriers to sustainability. Data collection from interviews and focus groups will ensure the comprehensiveness of findings and strengthen validity [50].

### Measures

All scales have good psychometric properties with similar populations. Listed below are the factors to be measured and instruments to be used, along with references to validation studies for the instruments.

Intake and baseline. Treatment center staff will document patient eligibility. Then patients will complete the baseline survey. They will report 12 demographic items (gender, age, race, education, etc.) and five items related to their opiate use history (age of first use, age of regular use, whether opioid use began with a physician-prescribed opioid, number of past quit attempts, and date of last use). Patients will also respond to items related to chronic pain diagnosis and treatment, current and past comorbid psychiatric diagnoses and treatment, pain severity (using the Numeric Rating Scale (NRS-11)) [51], and HIV/HCV status.

Dependent variable. Self-reported illicit opioid use days will be analyzed in 30-day periods. At baseline, a Timeline Followback (TLFB) [52] for the 30 days before admission will be obtained (with opioid use separated from other drug use) and a urine drug screen collected (CTN-approved drug use outcome measures). For follow-up assessments, the TLFB for the previous 120 days will be obtained. The TLFB has been successfully used to obtain drug use data for extended periods of time and with polydrug-using patients [53].

At months 4, 8, 12, 16, 20, and 24. During phone surveys after baseline data collection, patients will complete a 120-day TLFB [54] to document their illicit opioid and other nonprescribed drug and alcohol use as well as health service use during the past 4 months. Health service use will be collected for the categories listed under “Health service use and cost” below. Patients will also complete measures of: relapse risk (Brief Addiction Monitor [55], nine items); pain severity (NRS scale [56], one item); HIV/HCV screening and link-to-care status (testing status and if tested, result, and if positive, whether the patient saw a medical provider); risk behaviors (HRBS [57], five items); status of current housing (two items) and employment (three items on type of employment, hours worked); quality of life (The Satisfaction with Life Scale [58], eight items); rating scale for withdrawal (three items); self-reported medication adherence (Morisky Medication Adherence Scale: MMAS-4 [59], four items); and loneliness (three items). We will collect number of phones lost, stolen, or broken (research records). For retention in treatment, we will take the proportion of appointments attended from clinic records. We will also determine if participants are engaging in other forms of treatment outside of the treatment facility, such as seeing a therapist, working with a sponsor, or attending NA/AA meetings.

Mediators. Self-determination theory (SDT) constructs will be assessed as follows: autonomy, Treatment Self-Regulation Questionnaire [60] (six items); competence, revised Drug-Taking Confidence Questionnaire [61] (eight items); and relatedness, our own bonding scale (five items). Negative affect will be assessed by Positive and Negative Affect: PANAS [62, 63] (20 items), and self-stigma by the self-devaluation subscale of the self-stigma in substance abuse scale [64] (seven items).

Moderators: we will focus our evaluation on gender but also collect data on other potential moderators (SUD severity as determined by the treatment site at intake using DSM-V criteria, pain as determined by the NRS-11, withdrawal, and loneliness).

A-CHESS use. A-CHESS use will be collected in time-stamped log files and includes when a patient accessed A-CHESS, service(s) selected, duration of service use, pages viewed, messages posted versus received, and communication style and content of messages. Content will be subject to computer-automated content analysis to identify communication styles that may predict study outcomes. Cumulative use (number of pages viewed and days used) significantly predicted risky drinking days in the randomized trial of A-CHESS with alcohol-dependent patients [33]. We will also collect data on sources of other SUD-related information and support.

Health service use and cost. Our cost analysis is motivated by the potential that A-CHESS has shown to reduce the use of costly health services associated with relapse. (In a field test with US military veterans, A-CHESS users had substantially decreased rehospitalizations related to relapse.) Our approach to measuring and analyzing health use data is adapted from McCollister and French’s 2003 analysis of the economic benefit of addiction interventions [65]. We will use the following categories of health service use: emergency room visits, hospital detox (day), and short-term residential treatment (day). We will also track costs for all other hospital visits and stays (in addition to emergency room visits and hospital detox); urgent care visits for any reason (to which we will apply cost estimates derived from a national survey of urgent care clinics [66]; individual psychotherapy or psychiatric care; and self-reported outpatient addiction treatment services after relapse (using the categories of outpatient addiction care outlined by McCollister and French [64], to which we will apply cost estimates provided in the 2008 national survey of 110 substance abuse treatment programs by French et al., adjusted for inflation [67]). We will also collect self-reported use of other health services (e.g., dental care, primary care, chiropractor), following the approach by Bell et al., to assess the cost-effectiveness of supervised versus unsupervised buprenorphine-naloxone administration [68]. We will derive cost estimates for various types of health care use (e.g., emergency room visits, hospitalizations, primary care visits, etc.) using data from the American Hospital Association and the American Medical Association.

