**Methods/design:**

This unblinded study will randomly assign 440 patients to receive MAT + A-CHESS or MAT alone. Eligible patients will meet criteria for having an opioid use disorder of at least moderate severity and will be taking methadone, injectable naltrexone, or buprenorphine. Patients with A-CHESS will have smartphones for 16 months; all patients will be followed for 24 months. The primary outcome is the difference between patients in the two arms in percentage of days using illicit opioids during the 24-month intervention. Secondary outcomes are differences between patients receiving MAT + A-CHESS versus MAT in other substance use, quality of life, retention in treatment, health service use, and, related to HIV and HCV, screening and testing rates, medication adherence, risk behaviors, and links to care. We will also examine mediators and moderators of the effects of MAT + A-CHESS.

We will measure variables at baseline and months 4, 8, 12, 16, 20, and 24. At each point, patients will respond to a 20- to 30-min phone survey; urine screens will be collected at baseline and up to twice a month thereafter. We will use mixed-effects to evaluate the primary and secondary outcomes, with baseline scores functioning as covariates, treatment condition as a between-subject factor, and the outcomes reflecting scores for a given assessment at the six time points. Separate analyses will be conducted for each outcome.

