Missing data. In previous addiction work, we completed 85% of surveys at 4, 8, and 12 months. We anticipate greater reductions at months 16, 20, and 24, reaching about 65% by month 24. In previous studies, we have kept missing data on core items in a survey to about 2% and expect a comparable rate in this study. In addiction treatment, data are not likely to be missing at random (i.e., the probability that data are missing is related to what the data would have been had the data been observed). For example, some patients may not want to disclose opioid use in surveys. Because this may lead to biased parameter estimates for our models, we will identify missing data patterns and use pattern-mixture modeling to test the sensitivity of our longitudinal intervention analysis to missing data assumptions [74–77] and conduct other sensitivity analyses after imputing missing data with a range of clinically plausible values based on explicit assumptions for the missing data (e.g., best-case, worst-case; with and without multiple imputation) [78–80].

Intention-to-treat and subject noncompliance. Standard intention-to-treat (ITT) estimates the average treatment effect by comparing outcomes based on assignment to treatment, but ignoring use of the treatment. Because ITT estimates do not represent treatment efficacy under noncompliance (e.g., a patient is randomized to A-CHESS but does not use the system), we will address noncompliance by also estimating treatment effects only for compliers using as-treated, per-protocol [81], and CACE (Complier Average Causal Effect) [82].

Dropout rates. In our A-CHESS RCT with alcohol-dependent patients [33], 88 patients were using opioids as well as alcohol; 261 were not using opioids. We compared the post-test survey response rate of opioid-using patients to the response rate of patients who did not use opioids. The non-opioid-using patients’ response rates were 94.3% at 4 months; 90.6% at 8 months, and 86.7% at 12 months. The opioid-using patients’ response rates were 91.2%, 86%, and 79.1%. Response rates declined in a relatively linear fashion in both groups, with reductions of about 5 percentage points in each period. We assumed a 65% response rate at 24 months by continuing the drop off rate for each of the three periods from 79% to 74% to 69% to 64%. Hence, we believe it is likely that by the end of the study we will still be able to reach 65% of patients originally enrolled.

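### The follow-up TLFB always looks back 120 days, so as written a patient who misses a survey and later returns is not asked about the missed four months of the primary outcome

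*Protocol article*

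**What the plan says.** The primary outcome is the "percentage of days using illicit opioids during the 24-month intervention" (Protocol article, Abstract, Methods/design). Under Measures, in the paragraph on the dependent variable, "Self-reported illicit opioid use days will be analyzed in 30-day periods", and the look-back is fixed: "For follow-up assessments, the TLFB for the previous 120 days will be obtained". The paragraph on the follow-up months repeats it ("patients will complete a 120-day TLFB") and gives health service use the matching four-month look-back.

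The section Quantitative data collection sets the schedule of six surveys: "All subjects will complete follow-up surveys over the phone with the UW study coordinator at months 4, 8, 12, 16, 20, and 24". That section gives urine screens the role of validating self-report; it does not use them to fill blank days.

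On completeness, the Missing data paragraph under Data analysis says "In previous addiction work, we completed 85% of surveys at 4, 8, and 12 months", and then "We anticipate greater reductions at months 16, 20, and 24, reaching about 65% by month 24". It expects that data will probably not be missing at random, because some patients may be unwilling to disclose use. Its response is analytic: pattern-mixture models, best-case and worst-case values, and multiple imputation. Nowhere does the article lengthen the TLFB for a patient who returns after a gap.

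**The concern.** The look-back equals the survey interval, so each interview reaches back only to about the previous scheduled survey, whether or not that survey took place. A patient who returns after a gap is on the phone and answering a TLFB, but the questions stop at 120 days. The earlier window stays blank and is later filled by a model or an assumed value. A survey held late loses days at the start of its window in the same way.

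The affected quantity is the primary outcome. The affected windows are those where the protocol doubts that missingness is ignorable, so assumptions there matter most and cannot be tested from the observed data. No analysis plan can restore days that were never asked about.

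**Working it through.** **Inputs from the Protocol article.** 440 randomized; 35% attrition; six follow-up surveys; 120-day TLFB; 30-day analysis periods. Response: 85% at months 4, 8 and 12 (Missing data paragraph), 74% and 69% at months 16 and 20 (Dropout rates paragraph), 65% at month 24.

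**Plan's own figure.** 440 × (1 − 0.35) = 286, the number stated in the power section. It reproduces.

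**Coverage.** 6 × 120 = 720 days, and 24 × 30 = 720, so six on-schedule windows match 24 thirty-day periods. Surveys are about 730.5 / 6 = 121.75 days apart, so on-schedule windows do not overlap and no later TLFB reaches a missed one.

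**Loss per missed survey.** 120 days = 4 periods; 120 / 720 = 16.7%. Two misses: 240 days, 33.3%. Three: 360 days, 50%.

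**Expected missed days.** Missed shares are 0.15 + 0.15 + 0.15 + 0.26 + 0.31 + 0.35 = 1.37 surveys per patient.
- Per patient: 1.37 × 120 = 164.4 days; 164.4 / 720 = 22.8%.
- All patients: 440 × 164.4 = 72,336 of 440 × 720 = 316,800 person-days.

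**Recoverable part.** A month-24 miss has no later survey, so only earlier misses count: 1.37 − 0.35 = 1.02 surveys, or 1.02 × 120 = 122.4 days (17.0%). Let f be the share of these misses followed by a later completed survey. The protocol does not give f, so the range below is an assumption.

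| f (assumed) | Days per patient | Share of 720 days | Person-days, N = 440 |
|---|---|---|---|
| 0% (pure dropout) | 0 | 0% | 0 |
| 10% | 12.2 | 1.7% | 5,386 |
| 25% | 30.6 | 4.3% | 13,464 |
| 50% | 61.2 | 8.5% | 26,928 |
| 100% (ceiling) | 122.4 | 17.0% | 53,856 |

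**Sensitivity to the response rates.** With the opioid-user rates from the Dropout rates paragraph (91.2, 86, 79.1, 74, 69, 64%), the missed shares sum to 1.367: 164.0 days, 22.8%. The ceiling is (1.367 − 0.36) × 120 = 120.8 days, 16.8%. The result barely moves.

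**Precision.** Suppose windows within a patient have equal correlation ρ (assumption). The variance of a mean of k windows is then proportional to ρ + (1 − ρ)/k. Going from k = 6 to k = 5 raises the standard deviation of a patient's mean by 2.8% at ρ = 0.3, 1.4% at ρ = 0.5 and 0.7% at ρ = 0.7. Loss of power is therefore not the main cost; reliance on assumptions is.

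**The case against.** **The article may only be silent.** It gives the look-back for surveys held on schedule and does not discuss missed or late ones. A full protocol or interview manual could allow catch-up. This stands in part: a reader might infer that longer recall is forbidden, and the text does not say so. But 120 days is stated twice without exception, and an interviewer following it would not ask about the gap.

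**There may be nothing to recover.** The protocol speaks of attrition and a steady drop-off. If every miss is permanent, no later call exists. This stands, and it is why the range starts at zero.

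**Longer recall may be worse data.** The sentence "The TLFB has been successfully used to obtain drug use data for extended periods of time and with polydrug-using patients" supports extended recall in general but gives no maximum and does not validate 240 or 360 days by telephone. A patient unwilling to disclose at month 8 may under-report the same days at month 12. Equal recall length for everyone is a defensible choice. This is the strongest objection. It is met by flagging the older days: they can be dropped, which restores the 120-day dataset, whereas days never asked about cannot be added.

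**Stronger readings that the documents do not support.**
- *A biased treatment effect.* If 5% of windows were recovered, with use on 50% of days against 20% elsewhere, an arm's mean would move by 0.05 × 30 = 1.5 percentage points, or 0.015 × 30 = 0.45 days per month. All three inputs are assumed, and this is a shift in one arm. It cannot be set against the target difference of about three days per month, because similar loss in both arms largely cancels and the mixed model still uses a patient's other periods. The phone plan supplied only in the A-CHESS arm makes unequal loss conceivable, but no figure supports it.
- *Relapsing patients avoid surveys.* The protocol says only that some patients may not want to disclose use.
- *Gaps or double counting even on schedule.* The 720 against about 730 days is calendar rounding, and nothing says that days are not stored by date.

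**Conclusion.** The point holds as a data-collection rule that is fixed less well than it could be. It is neither a contradiction nor a wrong figure. Following the text, a returning patient's missed window is not asked about, and each such window is one sixth of the covered outcome. About 22.8% of person-days are expected to be missed, of which between 0% and about 17% of all person-days could be regained. The 17% is a bound, not an expectation: it requires every miss before month 24 to be followed by a completed survey.

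This rests on the protocol's projected response rates, on the return share being unknown, and on no unseen manual already providing catch-up. No bias in the between-arm difference has been shown or sized. The planned missing-data analyses remain appropriate for windows that truly cannot be observed; the point is to leave fewer windows to them.

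**What to change.** At each completed follow-up:

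1. Take the TLFB and the health service use questions back to the date of the last completed interview, instead of a fixed 120 days or four months.
2. Store use by calendar date and assign days to 30-day periods counted from randomization, so that late or early calls neither lose nor duplicate days.
3. Flag every day recalled from beyond 120 days, and repeat the primary analysis without the flagged days as a sensitivity analysis.

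If a manual already provides for this, one sentence in the protocol settles the matter.

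The cost is a change to the interview script and database, and a longer call only for patients who missed or delayed a survey. The downside is less precise recall, or continued non-disclosure, for the older days; step 3 shows whether it matters. Recruitment began in April 2016 and the article reports 23 participants at 8 June 2016, so no month-4 survey was yet due and the change could then have covered essentially all follow-up.
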